#### Project Timeline

This project will occur in 2 phases over 5 years. In phase 1 (year 1), we worked with our collaborators in New York State and West Virginia to tailor our protocols and procedures to their quitlines, refine our recruitment methods to each state’s smokers, refine all study (participant) materials to ensure that the demographics of each state are represented, and update our training materials to include state-specific data and issues that may be relevant to specific participant populations. We hired and trained all coaches to competency and user-tested all our systems and procedures. In phase 2, we will conduct the RCT. Recruitment, enrollment, T0 assessments, and the delivery of the intervention will occur during years 2 to 4. Follow-up assessments will occur during years 2 to 5, with data analyses and dissemination of the findings in year 5.

### Ethics Approval, Informed Consent, Data Protection, and Participation

This study has been reviewed and approved by the University of Arizona institutional review board (2103633455; principal investigator [PI]: JG). All participants complete an informed consent document either through REDCap or on the telephone with trained study staff. Potential participants may ask questions of study staff before signing the consent document. The consent document describes the study, expectations, risks, and benefits of study participation. All study data are housed in REDCap and University of Arizona Box Health. Both systems are encrypted and HIPAA compliant. Only trained study staff have access to participant data, and data are restricted to study staff by role on the project. Participants may receive up to US $125 for participating in all study activities. Participants receive US $10 for completing the T0 survey, US $15 for completing the 3-month survey, and US $25 for completing the 6-month survey. All participants who report 7-day abstinence at the 6-month assessment are asked to complete an expired CO test to biochemically verify abstinence. Participants who complete biochemical verification receive US $50. Some participants will be selected based on their responses to the 3-month survey and invited to participate in a semistructured interview. Participants who complete this interview will receive US $25.

## Results

The *Be Smoke Free* study was funded in September 2021 (National Center for Complementary and Integrative Health, R01AT011500; PI: JG). Recruitment started in August 2022, with a staggered start. The West Virginia and New York State quitlines and community recruitment were all active as of October 2022. As of March 31, 2023, a total of 242 participants had been enrolled in the study, surpassing our accrual goal of 240. The Arizona Smokers’ Helpline (ASHLine) contract was transferred to another vendor, and we lost this as a recruitment site. The New York State and West Virginia quitlines each agreed to recruit an additional 100 participants to compensate for the loss of 200 Arizona quitline participants.

Follow-up assessments began in November 2022. As of March 31, 2023, of the 118 participants who were eligible for the 3-month assessment, 97 (82.2%) completed the assessment, and 93% (26/28) of participants eligible for the 6-month assessment had completed it. Because of technical difficulties with the hardware and software, biochemical verification began in April 2023. Qualitative interviews began in April 2023. Recruitment will continue through 2025 and follow-up assessments through 2026. Primary results are expected to be published in 2027.

## Discussion

### Overview

Phase 1 of the study was conducted between October 1, 2021, and July 30, 2022, and completed successfully. The study team met weekly and updated the design, content, and formatting of the intervention quit booklets that were created for the pilot study. We also created recruitment materials, including digital and print media, featuring images representing various communities. We recruited 8 stakeholders from 3 states to form a CAB. We held general and state-specific CAB meetings to obtain feedback on recruitment and intervention materials, as well as recruitment plans and methods. We also updated and refined coach training materials, revised data collection materials from the pilot study, and created new data collection materials. We developed protocols for screening, contact attempts, biochemical verification, and other data collection procedures and programmed and tested them all in the REDCap database. We developed procedures for recording and storing coaching calls using new Zoom (Zoom Video Communications, Inc) technology and hired and trained 4 quit coaches and all research staff. We received institutional review board approval for all human participants study procedures and registered the study with ClinicalTrials.gov.

We began phase 2, conducting the RCT, in July 2022. We have experienced both challenges and successes in the first 6 months of the RCT. To date, we have recruited participants through the West Virginia and New York State quitlines and via study social media posts and posts from community partners in Arizona, New York State, and West Virginia. We designed and sent recruitment postcards to former New York State quitline clients, used display ads on Meta sites, advertised on radio stations in New York State and Arizona, and distributed rack cards and flyers to our CAB members and other contacts in the community (eg, physicians’ offices). We recruited our first participant in Arizona in July 2022, then opened recruitment in West Virginia in August 2022, and in New York State in September 2022. In September 2022, the ASHLine contract was transferred from the University of Arizona to National Jewish Health, and the Arizona Department of Health Services declined to collaborate on the rest of the study. The New York State Smokers’ Quitline agreed to increase recruitment to compensate for the loss of the ASHLine.

Potential participants who were referred by a quitline or found out about the study from community-based methods were contacted via telephone calls, emails, and SMS text messages and screened by study staff. Potential participants who met the eligibility criteria completed consent and T0 assessments on the web in REDCap and were randomized to 1 of 2 study conditions.

Randomized participants who scheduled and completed the first study visit (session 1) were considered *enrolled participants* in the study.

To ensure that we are meeting our goals and maintaining fidelity of all procedures, we review enrollment and recruitment progress at weekly study team meetings, monitor intervention fidelity in REDCap, and review call recordings on a monthly basis. Any discrepancies in fidelity are immediately corrected, and study personnel receive weekly feedback. Coaches attend individual monthly supervision sessions with the PI.

We are currently retaining >80% of the sample at 3 months and >75% at 6 months. This is similar to our pilot study [12] and compares favorably with other studies that are conducted entirely remotely [50]. If participants miss some data collection visits or drop out from the study after session 1, partial data will be captured for them. As indicated previously, mixed effects models will be used to model smoking outcomes. Mixed effects models have an inherent way to handle ignorable missing data mechanisms (ie, missing completely at random and missing at random), which can be accounted for based on the observed data. In addition, extensive efforts will also be made to maximize retention as well as minimize missing data, and reasons for dropping out and missing data will be recorded. If the missing data mechanism is suspected to be nonignorable (ie, missing not at random), a multiple imputation–based sensitivity analysis approach [51] will be used to evaluate the impact of missing data mechanisms on the intervention effect, where the sensitivity analysis parameter controls the missing mechanism, and the multiply imputed data will be analyzed using standard methods based on the established rules in Rubin [52] that account for uncertainty owing to missingness.

### Limitations

We experienced several challenges during the first year of the RCT. First, we lost one of our quitline partners. Despite many attempts to replace the ASHLine, we were unable to do so. Both the New York State and West Virginia quitlines agreed to compensate for our loss of the ASHLine. However, West Virginia experienced a drop-off in call volume and staffing shortages. Therefore, the New York State Smokers’ Quitline increased their recruitment to maintain accrual goals. Although the demographics of New York State are different from those of Arizona, we will continue to conduct community recruitment from Arizona so that we can examine treatment outcomes by state.

Second, the social media advertising and earned media (eg, interviews with news outlets) strategies were not as successful as in our pilot study. Therefore, we attempted to recruit using radio advertising. However, radio advertising was not effective either. We have engaged a recruiting firm to assist with community recruitment in Arizona. Despite these setbacks, we have consistently maintained our accrual goals. If needed, we have built in an additional 3 months in year 5 for continued recruitment.

Third, biochemical verification has been difficult for many participants because of inexperience using technology. Although study staff schedule Zoom sessions to *walk participants through* the data collection procedure, many of the participants find it difficult or impossible to complete the expired CO test. Therefore, self-reported 30-day abstinence is our primary outcome, and we will also examine 7-day self-reported and biochemically validated abstinence.

Finally, because the intervention is conducted entirely remotely with no person contact, we experience high attrition between randomization and the first treatment session. Therefore, we classify people as participants only after they have scheduled and completed their first treatment session, and all metrics regarding outcomes are reported for enrolled participants. Participants do not know to which condition they have been randomized until the first session. Therefore, we do not expect differential attrition before session 1 to cause bias while evaluating the intervention effects. Even if the differential attrition rate is not expected to relate to the intervention conditions, an inverse probability of attrition weighting approach [53] will be used to handle differential attrition rates and account for potential bias if attrition is indeed selective.

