#### RCT Protocol

The study protocol was adapted from our existing protocol [12,23]. Participant recruitment occurs during years 2 to 4 of the project, after coaches are trained and competent in the GIC and BC protocols. All screening, enrollment, and treatment activities are conducted by telephone, email, and SMS text message by research staff at the University of Arizona.

Recruitment occurs through quitlines and population-based activities. Quitline staff prescreen potential participants and describe the study to callers. Quitline staff collect eligible and interested callers’ contact information, including their telephone number, and transfer these data to project staff located at the University of Arizona. For population-based activities, potential participants recruited through population-based methods contact project staff.

For both recruitment methods, project staff contact interested callers within 1 business day. Project staff provide a detailed description of the study. Callers who are interested in participating are screened again for eligibility by project staff. Staff then consent eligible callers and administer the T0 survey or send survey links (REDCap) by SMS text message or email to participants who choose to complete the forms themselves. Those participants who complete the T0 survey are randomly assigned to the GIC or the BC via REDCap. Noneligible or noninterested callers are transferred back to their state quitline. Randomized callers are contacted by their study coach within 2 business days. Once callers complete their first session, they are considered enrolled participants in the study. All coaches are located at the University of Arizona. Participants in each condition receive 6 sessions, lasting from 10 to 60 minutes, depending on the condition and session topic.

All session activities and interactions with participants are managed and recorded in REDCap. Coach competencies and protocol fidelity are routinely monitored by the investigators. Process data (ie, coach notes and in-depth interviews) will be collected during the 6-week program and at T1.

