##### Enrollment

Potential participants are screened by trained study staff over the telephone or via REDCap. Eligible participants complete the T0 survey and informed consent over the telephone or on REDCap. Participants download the consent form from REDCap or request that study staff send them a hard copy. Study staff send condition-specific program materials to randomized participants. Ineligible callers are transferred back to the quitline in their state of residence using a *warm handoff* (ie, study staff call the quitline, talk to enrollment staff, and then transfer the caller directly to the quitline enrollment staff) or a HIPAA-compliant electronic process (eg, encrypted email).

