### Conclusions

The *Be Smoke Free* study is a first-of-its-kind RCT that incorporates GI into telephone-based tobacco cessation treatment. This study uses rigorous, transparent, and reproducible methods. The study protocols are based on strong theoretical frameworks and empirical evidence. We use best practices to address challenges in large studies with remote program delivery and data collection, well-established measures to reduce errors associated with self-report, successful recruitment and retention methods to reduce selection and nonresponse biases, and both intent-to-treat analysis and other methods to handle missing data.

Delivering a GI tobacco cessation intervention via telephone is a highly scalable novel integrative approach that may appeal to a broad range of smokers and increase the use of evidence-based tobacco treatment quitlines. This rigorous research has the potential for high overall impact. If successful, the *Be Smoke Free* program will have substantial benefits for the long-term health of people who use tobacco across the United States.

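### Outcomes are analysed only in people who completed session 1 after randomisation: this is a modified set, not intention-to-treat, and the argument that it causes no bias is not secured

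*Protocol article*

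**What the plan says.** Under RCT Protocol, people are randomised once they complete the T0 survey, and then "Randomized callers are contacted by their study coach within 2 business days". The same section adds: "Once callers complete their first session, they are considered enrolled participants in the study". Limitations concedes high attrition between these two points and states that "we classify people as participants only after they have scheduled and completed their first treatment session" and that "all metrics regarding outcomes are reported for enrolled participants".

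The reason given for expecting no bias is that "Participants do not know to which condition they have been randomized until the first session". Limitations also plans inverse probability of attrition weighting, in a sentence that ends with a condition about attrition being selective.

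Two other sections bear on that reason. Enrollment says: "Study staff send condition-specific program materials to randomized participants". Phase 1 says that four coaches were hired, two per condition, each delivering one protocol.

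On the label, Data Analysis (Hypothesis 1) presents the mixed models as in keeping with intention to treat, and Conclusions claims "both intent-to-treat analysis and other methods to handle missing data".

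**The concern.** Membership of the analysis set is decided after randomisation. A comparison restricted in this way keeps the protection of randomisation only if starting treatment does not depend on arm. The plan's first support for that is participants' unawareness of their arm. If materials naming the condition arrive before session 1, or if coaches tied to one arm differ in how persistently or how soon they reach people, the starters in the two arms may be different kinds of people.

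The primary 6-month abstinence comparison is at stake, and so is its label. A reader told that this is an intention-to-treat analysis would assume that everyone randomised is counted.

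**Working it through.** **1. Is the set intention-to-treat?** The order is T0 survey, randomisation, coach contact, session 1, enrolment. Outcomes are reported for the enrolled. T1 and T2 are timed from enrolment, so a randomised person who never starts has no defined assessment date. Under Discussion, Overview, partial data are provided for only when dropout follows session 1. Mixed models and imputation handle missing outcomes among the enrolled; they do not bring non-starters back. The set is modified, whatever one concludes about blinding.

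**2. The plan's own power figure.** Inputs from Power and Sample Size: 1200 participants, 20% dropout, 0.30 versus 0.40, uncorrected chi-square, two-sided 5%. Equal allocation is assumed. Per arm, n = 1200 × 0.8 / 2 = 480.

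z = [0.10 × √480 − 1.96 × √(2 × 0.35 × 0.65)] / √(0.30 × 0.70 + 0.40 × 0.60) = (2.191 − 1.322) / 0.671 = 1.295, so power is 0.902. The stated 90% is reproduced, and the sample-size arithmetic is not at fault.

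**3. How large could selection be?** The documents give no start rate by arm, so these inputs are assumptions: no true effect; 80% of BC start; enrolled BC quit rate 0.30; GIC starts g lower; the extra GIC non-starters would have quit at 0.15. The enrolled GIC quit rate is then

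q = (0.80 × 0.30 − 0.15 × g) / (0.80 − g).

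With 480 analysed per arm, SE = √(2 × 0.30 × 0.70 / 480) = 0.0296. The two-sided type I error is P(|Z| > 1.96) when Z is shifted by (q − 0.30) / SE.

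| Gap g | q | False difference | Shift | Type I error |
|---|---|---|---|---|
| 0 | 0.300 | 0 | 0 | 5% |
| 0.02 | 0.237 / 0.78 = 0.304 | 0.4 points | 0.13 | 5.2% |
| 0.05 | 0.2325 / 0.75 = 0.310 | 1.0 point | 0.34 | 6.3% |
| 0.10 | 0.225 / 0.70 = 0.321 | 2.1 points | 0.72 | about 11% |

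The direction favours whichever arm loses more poor-prognosis people, and could go either way. Any planned weighting is ignored here. Equal start rates remove the bias only if the same kind of people start in both arms, so baseline characteristics of starters matter as well as the rates.

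**4. What would counting everyone cost?** Assume that non-starters quit at 10% in both arms, starters at 0.30 versus 0.40, and follow-up loss is 20%. With a fraction a not starting, the difference becomes (1 − a) × 0.10. Power uses the formula in step 2.

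| Not starting | Rates | Difference | Power, 1200 randomised | Power, 1200 enrolled |
|---|---|---|---|---|
| 20% | 0.26 vs 0.34 | 0.08 | 0.77 | 0.86 (1500 randomised) |
| 40% | 0.22 vs 0.28 | 0.06 | 0.57 | 0.79 (2000 randomised) |

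Both power columns are shown because Study Design sets 1200 as the number randomised, while Results counts accrual on enrolled people.

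**The case against.** The sponsor discloses the restriction, gives a reason for it and names a remedy. Four stronger readings that a reader might infer go beyond the text.

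- **That participants are shown to be unblinded before session 1.** Enrollment gives no timing for the materials. Nor does the word randomised settle it, because the Discussion applies it to people who have already started: "Randomized participants who scheduled and completed the first study visit (session 1) were considered" enrolled. Materials could go out at or after session 1, consistently with Limitations. This is an ambiguity, not a proven contradiction.
- **That arm-specific coaches schedule session 1.** The text says only that the coach contacts people. Contact by someone who works in one arm is still enough for effort or availability to differ by arm, even if the participant is unaware.
- **That there is no protection against selection.** Weighting is planned, and the condition in that sentence may attach only to its last clause. The protection is still partial: no criterion for selective attrition is given, and weights use measured T0 variables, so unmeasured motivation would remain.
- **That the primary result will be biased.** Nothing in the documents shows a difference in start rates. If starting is independent of arm, the starters-only comparison is unbiased, as the sponsor expects.

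It is also fair that detailed analysis sets often sit in a statistical analysis plan that is not shown. That does not rescue an intention-to-treat claim that the article itself contradicts.

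**Conclusion.** The labelling point stands without assumptions: outcomes are restricted to session-1 completers, so the analysis is modified intention-to-treat, and the unqualified claims are wrong as written.

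The no-bias argument is weakened but not refuted, by the untimed dispatch of condition-specific materials and by pre-session contact from a coach who works in one arm. On the assumptions in the working, a gap in start rates of 5 to 10 points gives a false difference of about 1 to 2 points, and type I error of about 6% to 11%. With starting independent of arm, both excesses vanish. These figures illustrate a risk; they do not estimate a bias.

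The documents do not compel making all randomised people the primary set. That would dilute the effect and lower power, and is a judgement for the sponsor.

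**What to change.** 1. State when condition-specific materials are sent, and ensure that they are released only at or after session 1, so that the unawareness claim in Limitations is true.
2. Name the session-1-completer set as modified intention-to-treat, and remove the unqualified intention-to-treat statements from Data Analysis and Conclusions.
3. Always report loss between randomisation and session 1, and T0 characteristics, by arm. Always run the analysis weighted back to all randomised using T0 data, whether or not attrition is judged selective. T0 data exist for everyone randomised, so this is feasible.
4. Add an all-randomised sensitivity analysis using T0 data and any T2 responses that non-starters give through the existing REDCap links, with T2 timed in the same way in both arms. Imputation from T0 data shares the limit of weighting, in that it uses only measured variables, so actual responses from non-starters add the most.

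The cost is a change to when materials are released, use of survey links that already exist, some extra analysis and corrected wording. The all-randomised estimate will be diluted, which is acceptable in a sensitivity analysis.

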### Conclusions

The *Be Smoke Free* study is a first-of-its-kind RCT that incorporates GI into telephone-based tobacco cessation treatment. This study uses rigorous, transparent, and reproducible methods. The study protocols are based on strong theoretical frameworks and empirical evidence. We use best practices to address challenges in large studies with remote program delivery and data collection, well-established measures to reduce errors associated with self-report, successful recruitment and retention methods to reduce selection and nonresponse biases, and both intent-to-treat analysis and other methods to handle missing data.

Delivering a GI tobacco cessation intervention via telephone is a highly scalable novel integrative approach that may appeal to a broad range of smokers and increase the use of evidence-based tobacco treatment quitlines. This rigorous research has the potential for high overall impact. If successful, the *Be Smoke Free* program will have substantial benefits for the long-term health of people who use tobacco across the United States.

